#### Statistical analysis

All the data will be electronically processed. Original study questionnaires and forms will be entered and kept at the coordinator site (University of Toulon) in a secure and accessible place. After quality control of the database, statistical analysis will be performed.

Baseline comparisons between arms will be performed using univariate analysis of variance for continuous variables and chi2 test for categorical variables. An intent-to-treat analysis will be done. ST of the CIPRES interventional group will be compared to ST of the control group by using mixed-model analysis which allows assessing changes over time between groups within a repeated measures design with the determination of time effect (T0, T1), group effect (CIPRES, control) and, the interaction effect between time and group. Group, time and group-by-time interaction will be treated as fixed effects, and schools, classes and individuals will be considered as random effects. The analysis will be repeated on the secondary endpoints, using a linear mixed model for the continuous variables. Unadjusted and adjusted analyses controlling for potential confounders (e.g., age, sex) will be performed. In addition, a per protocol analysis will be carried out according to the adherence of classes to the intervention.

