### Statistical considerations

#### Sample size calculation

In a French study measuring ST with Actigraph GT3X accelerometers, children aged 7 to 10 accumulated 583 minutes on average (standard deviation: 57 min) of ST per day [76]. We will aim with the CIPRES intervention to reduce by 30 minutes per day the ST in the target population. To evaluate the number of subjects needed, we will choose α risk equal to 5% and β risk equal to 10% (power = 90%). Without considering clusters, showing a decrease of 30 minutes of ST per day between pre- and post-intervention will require to include 92 children per group (taking into account a correlation of 0.4 between baseline and follow-up measures). Randomization by cluster requires taking into account inflation factor of our sample size because of the homogeneity of the conditions within each cluster: 1+(m(1+cv^2^)-1)r (m being the average number of subjects per cluster, cv a coefficient of variation equal to the ratio between the standard deviation of the size of the clusters per m, and r being the intraclass correlation coefficient). In our study, the cluster is a municipality. With a potential average of 150 children included per municipality, a coefficient of variation at 0.5, and a rho coefficient set at 0.01 according to databases of intraclass correlation coefficients [77] and a recent French study [78], the inflation factor is equal to 2.87. The number of subjects needed to be able to show a difference of 30 minutes per day in ST is estimated at 527 children. Taking into account a potential rate of 25% of lost-to-seen over time, the number of subjects to include in the CIPRES study amounts to 700 children (i.e., 350 in the intervention group and 350 in the control group), corresponding to approximately 14 classes per group (i.e., approximately 7 schools per group).

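### The planned group-by-time test is in effect a change-score analysis; at the plan's own correlation of 0.4, adjusting T1 sedentary time for T0 would be more precise, by 30% down to 12% in variance depending on how stable cluster means are

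*Protocol article*

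**What the plan says.** The Statistical analysis section compares ST between arms with a mixed model for repeated measures at T0 and T1. "Group, time and group-by-time interaction will be treated as fixed effects", and schools, classes and individuals are random effects. T0 ST is therefore one of the two outcomes. It is not a covariate, and the arms may differ freely at T0. The adjusted analyses name age and sex as examples of confounders; T0 ST is not mentioned.

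The Sample size calculation section uses a French study in which "children aged 7 to 10 accumulated 583 minutes on average (standard deviation: 57 min) of ST per day", a target reduction of 30 minutes per day, 5% alpha and 90% power. It states that this "will require to include 92 children per group" without clustering, "taking into account a correlation of 0.4 between baseline and follow-up measures". It then applies a cluster inflation: "With a potential average of 150 children included per municipality, a coefficient of variation at 0.5, and a rho coefficient set at 0.01", so that "the inflation factor is equal to 2.87". This gives 527 children, and 700 after allowing for 25% loss.

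**The concern.** With two occasions and a free group difference at T0, the group-by-time term subtracts the whole baseline difference between arms. When a child's two measurements correlate at only 0.4, much of a T0 value is transient, and subtracting all of it adds noise. At child level, a chance T0 difference is expected to carry over to T1 by a fraction of 0.4, while a change score removes all of it. Regression adjustment removes only the part that carries over. With four randomised municipalities, chance imbalance at T0 is likely and precision is scarce. T0 accelerometry is planned anyway, so a more precise estimate may be available without new data.

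**Working it through.** **Inputs** (Sample size calculation section): SD 57, difference 30, alpha 5%, power 90%, correlation r = 0.4, m = 150, cv = 0.5, intraclass correlation 0.01. Sidedness is not stated. Two-sided reproduces the plan's figure; one-sided would give 75.

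**Step 1: the interaction is the difference in change.** On one simulated set of 184 complete pairs, the interaction from a mixed model with child random intercepts and the difference in mean change were both −39.065, with standard error 8.355.

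**Step 2: reproduce the plan.** With variance factor f, n per group = 2 × (1.96 + 1.2816)² × 57² / 30² × f = 75.86 × f.

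| Estimator | f at r = 0.4 | n per group |
|---|---|---|
| Change score | 2(1 − r) = 1.2 | 91.04, so 92 |
| T1 only | 1.0 | 75.86, so 76 |
| T1 adjusted for T0 | 1 − r² = 0.84 | 63.73, so 64 |

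Of the three, only the change score gives the stated 92. The inflation is 1 + (150 × 1.25 − 1) × 0.01 = 2.865, and 2 × 92 × 2.865 = 527. Then 527 / 0.75 = 703, stated as 700.

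**Step 3: the gain in the plan's own framework.** The ratio is 0.84 / 1.2 = 0.70, a 30% lower variance. In general it is (1 + r)/2: 0.65 at r = 0.3 and 0.80 at r = 0.6. At N = 527 with inflation 2.865, power under the plan's normal formula is 90.3% for change and 97.3% for baseline adjustment.

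**Step 4: what the inflation implies about clusters.** Let c be the correlation over time of the cluster effects. The intraclass correlation of the change score is 2 × 0.01 × (1 − c) / [2 × (1 − 0.4)] = 0.01 × (1 − c) / 0.6. This equals 0.01 only at c = 0.4. Applying 2.87 unchanged to the change-score size therefore implies c = 0.4, where the 30% carries over to the clustered design.

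**Step 5: other values of c.** The article gives no c, so I assume 0.4 to 1.0. Total r stays at 0.4, the intraclass correlation at 0.01, and clusters are of equal size m. With within-cluster correlation w = (0.4 − 0.01c) / 0.99, the variance factors are:

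- T1 only: V = 0.01m + 0.99
- Change: 0.02m(1 − c) + 1.98(1 − w)
- Best adjustment: V(1 − R²), with R = (0.01mc + 0.99w) / V
- Child-level slope only: 0.01m(1 + w² − 2wc) + 0.99(1 − w²)

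Results for m = 150:

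| c | T1 only | Change | Best adjustment (saving against change) | Child slope only (saving against change) |
|---|---|---|---|---|
| 0.4 | 2.49 | 2.99 | 2.09 (30%) | 2.09 (30%) |
| 0.6 | 2.49 | 2.39 | 1.82 (24%) | 1.85 (22%) |
| 0.8 | 2.49 | 1.80 | 1.47 (18%) | 1.62 (10%) |
| 1.0 | 2.49 | 1.20 | 1.06 (12%) | 1.39 (16% worse) |

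For m = 50, about one school (700 children in about 14 schools), the best saving runs from 30% to 20%. For m = 25, about one class (700 in about 28 classes), it runs from 30% to 24%.

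**The case against.** The strongest reply is that nothing here is wrong. The trial is sized for change and analysed for change, the stated 90% is met on the plan's own inputs, and a group-by-time test is standard. All of that stands, and it limits the point to efficiency.

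Three stronger readings are tempting, and the article does not support them.

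- **That the planned test is less precise than ignoring baseline.** The factors 1.2 and 1.0 suggest so, but they are child-level results. At m = 150 the order has already reversed at c = 0.6 (2.39 against 2.49), and at c = 1 the change score is far better (1.20 against 2.49). School and class random effects read as constant over time would imply c = 1 at those levels.
- **That adjustment is a free 30%.** The 30% needs c of about 0.4. If cluster effects are stable, a child-level slope alone can lose its advantage.
- **That a model forcing equal T0 means in the two arms would serve equally well.** The section on co-construction shows that the intervention communes were known at that stage, and schools and classes join voluntarily in phase 2. Randomising towns does not guarantee equal expected T0 means among children recruited afterwards, and forcing equality could bias the estimate.

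The last difficulty also touches baseline adjustment: if T0 differences are systematic, adjusted and change estimates can disagree, and neither is automatically right. That is a reason to report both. The confounder list is also given only as examples, so it does not exclude T0 ST. But the model as written already uses T0 ST as an outcome.

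**Conclusion.** The point holds as an efficiency improvement. For complete pairs the planned interaction is a change-score comparison. At r = 0.4 its variance factor is 1.2 against 0.84 for baseline adjustment, or 92 against 64 per group before clustering. The variance saving is 30% under the cluster correlation that the plan's inflation step implies. At m = 150 it falls to 12% if cluster effects are fully stable.

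These figures rest on r = 0.4, an intraclass correlation of 0.01, equal cluster sizes and a correctly specified adjustment at child and cluster level. The equivalence with a change score is exact only for complete pairs, and 25% loss is expected. With four municipalities, the gain at that level is uncertain. The planned analysis remains valid, and the smaller group size is no ground for recruiting fewer children.

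**What to change.** State as the primary estimate the group difference in T1 ST from a mixed model with these terms: group, the child's T0 ST, the cluster-level mean T0 ST (for example the school mean), and the cluster random effects. The cluster mean matters because a child-level slope alone can do worse than the change score when cluster effects are stable. Keep the group-by-time analysis as a prespecified sensitivity analysis, and say how a disagreement between the two would be read, given that schools and classes are recruited after allocation.

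The cost is analysis wording only; no new data are needed. The small downside is that children without T0 accelerometry leave the primary model unless T0 is imputed, so the handling of missing T0 values should be stated with the model.

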### Study design

The intervention will be evaluated by a two-armed prospective cluster-randomized controlled study. Randomization will attribute either the intervention group (i.e., receiving the CIPRES intervention) or the control group (i.e., no intervention), considering municipalities as clusters (i.e., all the classes of the same municipality belong to the same group) to avoid contamination between groups. The target population is made up of 700 French children enrolled in primary school (year 4 and 5) located in 4 municipalities in the Var department, southeast of France (i.e., Toulon, La Seyne-Sur-Mer, Hyères, Brignoles) (Fig 1).

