### Population

The targeted territories are four cities from southeast France next to the Mediterranean Sea (Var department) randomly assigned to intervention group (Toulon, Brignoles) or control group (La Seyne-sur-Mer, Hyères). The target population is made up of 700 children attending primary schools in these municipalities in the years 4 and 5 classes (aged 8 to 10 years old). This study will more broadly include the participation of key actors who are in contact with children or likely to play a role in the organization of school, extracurricular and family time for children, namely teachers (school time), educators including association staff and municipal staff (extracurricular time), and the parents of children (family time). The schools will be selected with the help of pedagogical advisors of the French National Education and then be contacted by the Health Education Committee of the Var department (the CODES 83). Schools and then classes will be recruited within the included municipalities, on a voluntary basis. For each class willing to participate in the study, parents receive a written note which includes explanations about the research’s aims, the assessment methods (i.e., self-administered questionnaires for children and their parents, and accelerometers worn by children for 7 days at T0 and T1), and that participation is based on their own volition. Children are given consent forms to take home for their parents to sign. Parents have the choice of ticking three types of consents: (i) parents’ consent to filling in the questionnaires; (ii) parents’ consent to children filling in the questionnaires; (iii) parents’ consent to children wearing accelerometers. Only children whose parents have given their consent will be included (Fig 2).

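### The primary mixed model has no term for municipality, the randomised unit, so on its plain reading the group-by-time test ignores the clustering for which the sample was inflated 2.87-fold

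*Protocol article*

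**What the plan says.** - **Randomised unit.** The Study design section randomises municipalities, so that "all the classes of the same municipality belong to the same group". The Population section names four towns, two allocated to each arm.
- **Sample size.** The Sample size calculation section says "In our study, the cluster is a municipality". It starts from 92 children per group, applies an inflation factor of 2.87 (150 children per municipality, coefficient of variation 0.5, intraclass correlation 0.01), reaches 527 children, and recruits 700 to allow for 25% loss.
- **Primary analysis.** The Statistical analysis section says "Group, time and group-by-time interaction will be treated as fixed effects", and that "schools, classes and individuals will be considered as random effects". Municipality is absent from both lists. The section does not say whether the random effects are intercepts only or include time slopes, and it gives no rule for degrees of freedom.

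**The concern.** The article does not leave the random effects to another document. It lists them, and the list omits the level that was randomised and that the sample size pays for.

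The effect of interest is the difference between arms in change from T0 to T1. Anything that moves sedentary time in one town over those six weeks and not in another adds error to that difference. Examples are local events, which Table 1 includes as a community-level strategy, or different measurement windows; the latter is my inference, not something stated. With two towns per arm, such a shift cannot be told apart from an intervention effect unless between-town variation enters the standard error. If it does not, the p-value and confidence interval for the primary outcome are too optimistic.

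**Working it through.** **1. Reproduce the plan's figures** (Sample size calculation section: SD 57, difference 30, correlation 0.4, alpha 5%, power 90%).

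- SD of change = 57 × √(2 × (1 − 0.4)) = 62.44 min/day.
- n per group = 2 × (1.960 + 1.282)² × 62.44² / 30² = 91.04, rounded up to 92. This is the plan's figure, so alpha is two-sided and the calculation is on change. A one-sided test would give 75, and a baseline-adjusted analysis 64.
- Inflation = 1 + (150 × (1 + 0.5²) − 1) × 0.01 = 2.865, printed as 2.87.
- 184 × 2.865 = 527; 527 / 0.75 = 703, printed as 700.

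The arithmetic is sound. It multiplies a change-based n by the factor, so it treats 0.01 as the intraclass correlation of change.

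**2. What the listed model tests.** With complete data, a school, class or child intercept has the same value at T0 and T1 and drops out of the child's change. As a check, four data sets were simulated and fitted with school and child intercepts. The group-by-time statistic matched a child-level two-sample t test on change to four decimals each time (for example 1.0301 and 1.0301). A class intercept, or a municipality intercept, would cancel in the same way.

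**3. False-positive rate if the inflation is ignored.** Rate = 2 × (1 − Φ(1.96 / √D)), where D is the inflation factor.

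| Correlation of change | 527 children, equal towns (m = 131.75, cv 0) | 527 children, cv 0.5 | Plan's m = 150, cv 0.5 |
|---|---|---|---|
| 0.001 | 6.5% | 6.9% | 7.2% |
| 0.005 | 12.7% | 14.6% | 15.9% |
| **0.01** | **19.7%** | **22.7%** | **24.7%** |
| 0.02 | 30.3% | 34.3% | 36.7% |

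In the last column at 0.01 the standard error is too small by √2.865 = 1.69. Simulations of four towns totalling about 527 children at 0.01 gave about 19.5% to 22.6%, depending on how unequal the towns were.

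**4. If 0.01 is a single-time-point correlation instead.** The correlation of change is then 0.01 × (1 − c) / (1 − 0.4), where c is the correlation of a town's effect between T0 and T1. With cv 0.5 and m = 131.75 to 150, the rate is:

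- c = 1: 5%
- c = 0.9: 8-9%
- c = 0.8: about 12%
- c = 0.4: 23-25%
- c = 0: 31-33%

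**5. If schools have random time slopes but municipality is still absent.** Two simulations with 7 schools per arm, testing school mean changes at correlation 0.01, gave 14.7% and 18.1%.

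**6. Test on the randomised unit.** A t test on four municipality mean changes (2 df) held 5.1% in simulation. Its power for 30 min/day with 527 children follows from:

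- SE = 62.44 × √(4 × 2.865 / 527) = 9.21, so 30 / 9.21 = 3.26. Against a normal reference, power is 90%. Against t on 2 df (critical value 4.30), it is 43%.
- With equal towns, SE = 8.26 and power is 50%.
- The 95% half-width is 4.30 × 9.21 ≈ 40 min/day. The child-level test would report 1.96 × 62.44 × √(4 / 527) ≈ 11 min/day.

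**The case against.** **The article does not say intercepts.** A reader might infer that the model is stated to have random intercepts only and that none of the clustering reaches the standard error. The text says only that the units are random effects, and covariance structure is something a condensed article may leave elsewhere. This stands, so the cancellation argument is conditional. It does not rescue the plan: slopes for schools or classes leave the randomised level out, and 15-18% remains.

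**The size is not fixed by the document.** A reader might take a narrow figure of 23-25% as established. That range comes from the formula with coefficient of variation 0.5; equal towns with 527 children give just under 20%. The source of the 0.01 is not visible here, and the section does not say whether it refers to change or to one time point. If town effects are very stable over six weeks, the excess is small, and at perfect stability there is none. So one cannot say that the test is invalid whatever the data. What can be said is that the plan inflates for this variation and then does not allow for it in the analysis.

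**The remedy is expensive.** A reader might think that only wording changes. The loss of power and the difficulty of estimating a variance from four towns are real. They follow from randomising four units and do not justify leaving the unit out.

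**Conclusion.** The point holds, as a contradiction between the design and sample size sections on one side and the analysis section on the other. The randomised unit is missing from the primary model. If the listed effects are random intercepts and 0.01 is the intraclass correlation of change, the two-sided type I error is about 20-25% instead of 5%. With 527 children it is about 13-15% at a correlation of 0.005 and about 30-34% at 0.02. It is 5% if municipality effects do not change over time. Because this affects the primary test, it should be settled before results are read.

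**What to change.** Base the primary inference on the municipality, in one of two ways fixed in advance:

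1. Analyse the four municipality mean changes in sedentary time by a two-sample t test on 2 df. This is the simpler choice. It weights towns equally and relies on approximate normality of four means.
2. Keep the mixed model and add a municipality-by-time random effect, with school-by-time and class-by-time effects where they can be estimated. Test group-by-time with small-sample degrees of freedom (Kenward-Roger or Satterthwaite). A municipality intercept alone is not enough, because it cancels. State what happens if the municipality-by-time variance is estimated as zero, since the model would then lose its allowance for towns.

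A permutation test cannot replace these: four towns split two against two in 6 ways, so the smallest two-sided p-value is 2/6 = 1/3.

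Keep the present model as a sensitivity analysis, labelled as conditional on these four towns, and state whether its random effects are intercepts or slopes.

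**Cost.** No new data are needed, but the 90% power in the Sample size calculation section must be restated. With 527 children and the plan's own values it is about 43-50% on 2 df, the interval will be wide, and variance components from four clusters will be poorly estimated. More children in the same four towns would help little, because the 2 df are set by the number of towns.

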**Fig 1 pone.0302556.g001:**
[figure not shown]
Design of the CIPRES cluster randomized controlled trial.

The study includes two phases: 1) co-building of a SB prevention intervention using a participatory approach, and 2) implementation and evaluation of the intervention.

Phase 1: The SB prevention intervention was co-build by using a participatory approach including representatives of each "level" of the SEM (i.e., children, parents, teachers, pedagogical advisors, staff from associations and municipalities). Volunteers from each level of the SEM were proposed to join an advisory committee to create an intervention with a participatory approach. Researchers were asked to propose scientific levers (e.g., multilevel approach, school environment, motivation-related variables and potential behavior change levers based on the TCM) and the other participants (i.e., children, parents, teachers, pedagogical advisors, staff from associations and municipalities) brought field experience and propositions regarding forms of action and adaptation to the context [47].

Phase 2: School and classes recruitment and implementation of the intervention started the 1st of September 2021 and is currently on going. In line with the French education system’s timetable, the intervention must last a minimum of six weeks, i.e., the time between two school vacation periods, in each recruited class and aims to reduce SB at different times in the child’s life: school, extracurricular and home. An evaluation of the effectiveness of the intervention is carried out before (T0) and after the intervention (T1: T0 + 6 weeks). Children’s ST is measured during everyday lifetime by accelerometers worn during seven days. Other variables such as the level of PA, declared BMI, ScT habits, and variables of TCM (i.e., autonomous motivation, attitudes, norms, perceived control, intentions) are also measured (Fig 1).

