Since the socioeconomic characteristics of children and their parents have been associated with children’s SB and PA in previous surveys [8], the deprivation level of each school location is collected. The Ecologic Deprivation Index (EDI) measures the level of deprivation at the smallest French geographical units [48]. The EDI is divided into quintiles (Q), from the lowest level of deprivation (Q1) to the highest (Q5). In France, children must attend the closest school to their home. So, the use of school EDI classification also provides information on the level of deprivation of pupils’ families. Thus, EDI will be used to investigate the effect of the intervention according to the level of deprivation of the school location.

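### Entered as main effects, age and sex cancel from the group-by-time contrast, so the adjusted analysis would agree with the unadjusted one almost automatically

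*Protocol article*

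**What the plan says.** The Statistical analysis section compares the arms with a mixed model "which allows assessing changes over time between groups within a repeated measures design". Its terms are given: "Group, time and group-by-time interaction will be treated as fixed effects, and schools, classes and individuals will be considered as random effects". There are two visits, T0 and T1, six weeks apart. The adjustment is then described in one sentence: "Unadjusted and adjusted analyses controlling for potential confounders (e.g., age, sex) will be performed". The same analysis is to be repeated for the continuous secondary endpoints.

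Two other statements in the Study design section bear on this. The article explains why it collects the EDI of each school location: "Since the socioeconomic characteristics of children and their parents have been associated with children’s SB and PA in previous surveys". It gives the index a use: "EDI will be used to investigate the effect of the intervention according to the level of deprivation of the school location". On the calendar it says: "School and classes recruitment and implementation of the intervention started the 1st of September 2021 and is currently on going". Each class is followed between two school holidays, so classes are measured in different school periods. Period is not named as a covariate anywhere.

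**The concern.** An adjusted analysis is meant to show whether the estimate survives control for confounders. Here the estimate is a difference between arms in within-child change. The two covariates named do not vary in a useful way within a child over six weeks: sex is fixed, and every child ages by the same amount, which the time effect absorbs. If they enter as main effects, they are adjusting a quantity from which they have already vanished.

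What is at stake is how the result is read. A report showing nearly equal unadjusted and adjusted effects invites the conclusion that confounding was examined and found unimportant. In fact the agreement would follow from the form of the model. Confounding of change, the only kind that can bias this contrast through a time-fixed covariate, would not have been addressed. With four towns, two per arm, and schools and classes that volunteer, randomization cannot be relied on to balance such factors.

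**Working it through.** **1. Which contrast the plan uses.** Inputs from Sample size calculation: SD 57 min/day, difference 30, correlation 0.4, alpha 5% (taken as two-sided), power 90%. With n = 2(1.960 + 1.282)²V/30², where 2(1.960 + 1.282)² ≈ 21.01:

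- Change score: V = 57² × 2(1 − 0.4) = 3898.8, n = 91.04, so 92 per group. This is the stated figure.
- T1 only: V = 57² = 3249, n = 75.9, so 76.
- T1 adjusted for T0: V = 57²(1 − 0.4²) = 2729.2, n = 63.7, so 64.

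The remaining steps also reproduce: 1 + (150 × 1.25 − 1) × 0.01 = 2.865; 184 × 2.865 = 527; 527/0.75 = 703, against a stated 700. Of the three forms only the change score gives 92, so sample size and model both rest on within-child change.

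**2. Algebra.** Let G be group, t visit (0 or 1) and x a time-fixed covariate:

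y(i,t) = b0 + b1·G + b2·t + b3·G·t + c·x(i) + school + class + child + e(i,t).

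Subtracting visits: y(i,1) − y(i,0) = b2 + b3·G + e(i,1) − e(i,0).

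The term c·x has gone. With both visits present for every child, the estimate of b3 is the difference in mean change, whatever x is and however unbalanced it is. If x·t is added with coefficient d, the difference becomes b2 + b3·G + d·x + error, and b3 is then adjusted. In a model of T1 on T0 with slope k, x keeps the coefficient d + (1 − k)c, so it also adjusts.

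**3. Numerical check, complete pairs.** Simulated data, with these assumptions: 14 schools, 28 classes of 25, 700 children; SDs 6 (school), 5 (class), 34 (child), 44 (residual), which give a total SD of 56 and a visit correlation of 0.39; true effect −30; effects on level of 12 min per year of age, 15 for sex and 4 per EDI quintile; arms unbalanced on all three. Generalized least squares for group-by-time:

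| Model | Estimate | SE |
|---|---|---|
| Unadjusted | −26.818 | 4.704 |
| + age, sex | −26.818 | 4.704 |
| + age, sex, EDI | −26.818 | 4.704 |
| + age, sex and their time interactions | −26.932 | 4.937 |

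The SE agrees with √(2 × 44² × 2/350) = 4.704.

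**4. With 25% of T1 removed at random.** The same design gave −27.30 unadjusted and −27.51 with age and sex. Over 20 repeats the absolute shift averaged 0.19 (maximum 0.71). A separate REML simulation of 30 repeats gave 0.18 (maximum 0.89), with an SE of about 5.2. Adding EDI and period as main effects as well gave 0.28 (maximum 1.12).

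**5. What would adjust.** One REML data set, complete pairs, true effect −30, arms unbalanced on EDI:

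| Assumed EDI trend | Unadjusted | + age, sex | + EDI, period as main effects | EDI × time |
|---|---|---|---|---|
| 0 | −36.98 | −36.98 | −36.98 | −33.93 |
| 6 min per quintile | −24.13 | −24.13 | −24.13 | −33.93 |

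Main effects never move the estimate. The interaction model gives the same answer whatever the trend, which is what adjustment should do; its SE rises from 4.66 to 5.93. The shift of 12.86 in the unadjusted column implies an EDI difference between arms of 12.86/6 ≈ 2.1 quintiles. That is a severe imbalance, so the table illustrates the mechanism and does not predict a bias for this trial.

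**The case against.** The strongest reply is that the article does not say covariates enter as main effects. Coding is commonly left to the analysis plan, and age-by-time or sex-by-time terms would adjust. That stands, and the point is conditional on it. It does not dispose of the point: the article itself sets out the model terms and names the example covariates, and the ordinary reading of the two together cannot do the stated job.

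A second reply is that the estimates will not be identical at 25% loss, and that the model also yields a group effect which covariates can alter. Both are true. But the shift is small against the SE, and in this parameterization the group term is the difference at T0, not the intervention effect.

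Three stronger readings are tempting and are not supported:

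- A reader might infer that EDI is excluded. It is not: the covariate list is open, and EDI has a planned use in examining the effect by deprivation level. An analysis of that kind in this model would normally carry EDI-by-time.
- A reader might infer that imbalance in deprivation passes directly into the estimate. It does not: an effect of EDI on the level of sedentary time cancels just as age and sex do. The cited associations are with behaviour, and no figure is given for six-week change.
- A reader might attach a bias in minutes to school period. The article gives no seasonal drift and does not say that the arms differ in period. If they differed completely, period could not be separated from arm and no covariate would help.

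**Conclusion.** The point holds in conditional form. If time-fixed covariates enter as main effects, the adjusted and unadjusted group-by-time estimates are equal with complete pairs. That result is algebra and needs no assumption about effect sizes or imbalance. At the planned 25% loss, age and sex shift the estimate by about 0.2 min/day on average and by less than 1 at most; this rests on the simulated variances and on T1 missing at random. The same cancellation applies to EDI and school period as main effects.

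The primary estimate is not shown to be biased. The defect is that the planned adjustment would be uninformative and could be mistaken for a robustness check. Whether EDI or period predicts change is plausible but not quantified in the article. This is worth correcting before analysis.

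**What to change.** Specify one adjusted analysis in advance: T1 sedentary time on T0 sedentary time, group, age, sex, school EDI (for example as one ordinal term) and school period of measurement, keeping the cluster random effects. If the repeated-measures form is kept, enter each covariate together with its time interaction. Apply the same form to the continuous secondary endpoints.

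The change is one of wording. EDI is already collected, and measurement dates should be on file because visits are scheduled by class. Adjusting for T0 also gains precision at the assumed correlation of 0.4: 64 against 92 per group before clustering.

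The costs are a few degrees of freedom, some at school level, and a wider SE where a covariate is strongly unbalanced. Children without T1 contribute nothing to a T1-on-T0 model. Two limits should be stated alongside it: with four towns no such model can remove town-level differences in trend, and period can be adjusted for only where both arms are measured in the same periods.
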